# SAFETY REPORTING

## Definitions

**Adverse Event (AE)** - is any untoward medical event that occurs to a study participant during the course of the study whether or not that event is considered related to the study drug. An AE can, therefore, be any unfavorable and unintended sign (including an abnormal laboratory finding, for example), symptom, or disease temporally associated with the study drug, whether or not considered related to the study drug.

Stable chronic conditions, such as arthritis, which are present prior to clinical trial entry and do not worsen are not considered AEs and will be documented in the subject’s clinical chart as medical history.

Clinical or laboratory events are considered adverse events only if they occur after the first dose of study treatment (see below for repor ting of adverse events).

Serious Adverse Events - An AE is considered to be "serious" if it results in one of the following outcomes

- Death,
- Life-threatening event (the subject was at immediate risk of death at the time of the event; it does not refer to an event which hypothetically might have caused death if it were more severe),
- Inpatient hospitalization (new admissions) or prolongation of existing hospitalization (beyond what is expected for normal clinical care)
- Persistent or significant disability/incapacity (a substantial disruption of a person's ability to conduct normal life functions),
- Congenital anomaly/birth defect

Any pregnancy which occurs during the trial treatment period will be followed until outcome. Any congenital abnormality or birth defect will be recorded as a serious adverse event.

**Unexpected Serious Adverse Events** - are untoward medical events which fit one or more of the criteria for SAEs above and which are not considered a part of normal clinical progression of disease or an expected reaction to standard treatment therapy. Any event that becomes of concern to the investigators or study doctors during the course of the trial may be reported as a USAE.

## Assessment of Adverse Events

Adverse events will be graded according to the Common Terminology Criteria for Adverse Events (CTCAE) definitions: <http://ctep.cancer.gov/protocolDevelopment/electronic_applications/ctc.htm>. In the event that an adverse event is not described within the CTCAE definitions, the following generic severity grading will be used:

**Grade 1 Mild;** asymptomatic or mild symptoms; clinical or diagnostic observations only; intervention not indicated.

**Grade 2 Moderate;** minimal, local or noninvasive intervention indicated; limiting age-appropriate instrumental Activities of Daily Living (ADL)*.

**Grade 3 Severe or medically significant but not immediately life-threatening;** hospitalization or prolongation of hospitalization indicated; disabling; limiting self care ADL**.

**Grade 4 Life-threatening consequences**; urgent intervention indicated.

*Instrumental ADL refer to preparing meals, shopping for groceries or clothes, using the telephone, managing money, etc.

**Self-care ADL refer to bathing, dressing and undressing, feeding self, using the toilet, taking medications, and not bedridden.

[Note: “Life-threatening” as a severity grade is not necessarily the same as “life-threatening” as a “serious” criterion used to define a serious adverse event. The former is a “potential” threat to life and the latter is an “immediate” threat to life.]

A laboratory abnormality only needs to be recorded as a clinical adverse event if it is associated with an intervention. Intervention includes, but is not limited to, discontinuation of a current treatment, dose reduction/delay of a current treatment, or initiation of a specific treatment. In addition, any medically important laboratory abnormality may be reported as an adverse event at the discretion of the investigator. This would include a laboratory result for which there is no intervention but the abnormal value suggests disease or organ toxicity. Laboratory events will be graded according to CTCAE definitions.

If clinical sequelae are associated with a laboratory abnormality, the diagnosis or medical condition should be reported as the adverse event (e.g., renal failure, haematuria) - not the laboratory abnormality (e.g., elevated creatinine, urine RBC increase).

The relationship of each adverse event to the trial medication must be determined by a medically qualified individual according to the following definitions:

**Related**: The adverse event follows a reasonable temporal sequence from trial medication administration. It cannot reasonably be attributed to any other cause.

**Not Related**: The adverse event is probably produced by the participant’s clinical state or by other modes of therapy administered to the participant.

Patients will be under active surveillance for adverse events. All adverse events will be scored as not related, possibly related, or related to the study drug. The events listed below, and any others agreed between the treating doctor and Principal Investigator, are recognised adverse reactions to aspirin may be considered related to the trial intervention:

**Blood and lymphatic system disorders** - anaemia, haemolytic anaemia, hypoprothrombinaemia, thrombocytopenia, aplastic anaemia, pancytopenia, prolonged bleeding time, occult blood loss, elevated transaminase levels, agranulocytosis.

**Gastrointestinal disorders** - gastrointestinal bleeding, erosions, perforations or ulceration which can occasionally be major (may develop bloody or black tarry stools, severe stomach pain and vomiting blood), gastrointestinal irritation (mild stomach pain, heartburn, vomiting and nausea).

**Hepatic disorders** - hepatitis (particularly in patients with SLE or connective tissue disease)

**Renal and urinary disorders** – disturbances of renal function

**Ear and labyrinth disorders** - tinnitus

**Salicylism**- mild chronic salicylate intoxication may occur after repeated administration of large doses, symptoms include dizziness, tinnitus, deafness, sweating, nausea, vomiting, headache and mental confusion.

**General disorders and administration site conditions** – Allergic reactions: rhinitis, urticaria, purpura, Stevens-Johnson syndrome, angioneurotic oedema, angio-oedema, asthma, worsening of asthma, bronchospasms.

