## Primary and Secondary Endpoints/Outcome Measures

The primary safety endpoint will be the occurrence of clinically significant upper-gastro-intestinal bleeding and any cerebral bleeding confirmed by brain imaging by 60 days from randomisation.

Clinically significant upper gastro-intestinal bleeding will be defined as any one of the following:

1. Vomiting fresh or changed blood of any volume
2. Melena
3. Unexplained drop in haemoglobin concentration of >2g/L
4. Greater than 5mls of fresh or changed blood aspirated from nasogastric tube

The primary efficacy endpoint will be any new MRI-proven brain infarction or death by 60 days. To assess this endpoint MRI will need to be taken at baseline and at 60 days from randomisation. The scans will be read by an independent neuroradiologist blind to the treatment allocation.

The secondary endpoints will be:

- Number of grade 3&4 and serious adverse events by day 60 from randomisation
- Time to death during 240 days from randomisation
- Duration of hospital stay
- Neurological disability (as assessed by the modified Rankin score and Glasgow outcome score) by days 60 and 240.
- Resolution of CSF inflammation by day 30 through measurement of CSF leucocytes, protein, glucose, cytokines (TNF-α, IL-1β, IL-8, IL-10, IFNγ) and eicosanoids (15-epi-Lipoxin, Lipoxin A4, LTB4, PGE2, TBXB2, PGD2).
- Antimicrobial activity of peripheral blood monocyte/macrophages on day 240 compared to baseline.
- The proportion of patients with MRI-proven infarction by day 240
- Concentration-time profile of salicylic acid including exposure, peak levels, half-life, elimination clearance and volume distribution

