## Adverse Event Recording

All adverse events which initiate after administration of the first dose of study drug and before the end of study day 60 will be recorded in the CRF. Events which are grade 3 and 4 adverse events and those judged to be possibly related or related to the trial intervention will be followed to resolution.

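### Whether a grade 3-4 laboratory value with no intervention and no clinical sequelae counts toward the grade 3-4 adverse-event endpoint is left to the investigator, while sections 6.4.6 and 8.3 say all adverse events are recorded

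*Protocol*

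**What the plan says.** All references are to the protocol.

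- **Section 8.1 (Definitions)**: "An AE can, therefore, be any unfavorable and unintended sign (including an abnormal laboratory finding, for example". A later sentence limits events to those after the first dose, "Clinical or laboratory events are considered adverse events only if they occur after the first dose of study treatment", and points forward to the reporting rules.
- **Section 6.4.6 (Subsequent Assessments)**: all adverse events are to be documented, followed and assessed for relation to aspirin. Laboratory findings are not excepted.
- **Section 8.3**: the rule for entries in the CRF is "All adverse events which initiate after administration of the first dose of study drug and before the end of study day 60 will be recorded". Again there is no laboratory exception and no reference to 8.2.
- **Section 8.2 (Assessment of Adverse Events)**: "A laboratory abnormality only needs to be recorded as a clinical adverse event if it is associated with an intervention". The list of interventions is open-ended. Beyond this duty, "any medically important laboratory abnormality may be reported as an adverse event at the discretion of the investigator". The scope of that option is spelled out: "This would include a laboratory result for which there is no intervention but the abnormal value suggests disease or organ toxicity". If there are clinical sequelae, the diagnosis is reported in place of the laboratory value. Laboratory events are graded by CTCAE.
- **Section 5.2**: one secondary endpoint is "Number of grade 3&4 and serious adverse events by day 60 from randomisation".
- **Section 9.2**: adverse-event frequency per arm is described, with no test attached.

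**The concern.** The instructions on what a site must write down are not the same. Sections 6.4.6 and 8.3 read as complete recording. Section 8.2 reads as a minimum duty plus discretion. The difference falls on a class of events that matters for this drug: section 8.2 lists anaemia, thrombocytopenia, occult blood loss, raised transaminases and disturbed renal function among recognised reactions to aspirin, and some of these may show first, or only, in a blood result.

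The primary objective is pilot safety data on two aspirin doses. If the grade 3-4 count depends partly on whether a clinician acted or chose to report, it is a less uniform measure of laboratory toxicity than the scheduled blood tests would allow. The data safety and monitoring board is affected too. Its planned tables in section 8.5 list baseline characteristics, serious and other adverse events, and event reports, so a laboratory abnormality never recorded as an event need not reach it by that route.

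**Working it through.** The protocol states no figure on this point, so the check sets the rules side by side for one case: a CTCAE grade 3-4 laboratory value arising after the first dose and before the end of day 60.

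| Situation | 8.1 with 6.4.6 and 8.3, read literally | 8.2 |
| --- | --- | --- |
| Associated with an intervention | Recorded | Must be recorded |
| Clinical sequelae present | Recorded | Recorded under the diagnosis |
| No intervention, no sequelae, investigator reports it as medically important | Recorded | Recorded, by choice |
| No intervention, no sequelae, investigator does not report it | Recorded | Not recorded, and 8.2 is still followed |

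Only the last two rows are in play. There, two investigators with the same result can both comply with 8.2, and one adds an event to the endpoint while the other does not.

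**How far section 7.9 narrows the gap.** Study treatment stops for grade 3-4 events considered related to aspirin. Stopping a treatment is an intervention under 8.2, so a value judged related becomes mandatory to record. But the protocol calls an event related only when no other cause can reasonably explain it. For a raised transaminase in a patient who also has severe disease and takes anti-tuberculosis drugs, that is hard to satisfy. The values left to discretion are therefore largely those with a competing explanation, for which a comparison between arms is more informative than a case-by-case judgement.

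**Direction and size.** For the values with no intervention and no sequelae, let *p* be the true risk in an arm and *s* the share that investigators choose to record.

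- Recorded risk in an arm: *s* × *p*.
- Recorded difference between two arms with the same *s*: *s* × *p*1 − *s* × *p*0 = *s* × (*p*1 − *p*0), which is smaller than the true difference when *s* < 1.
- Recorded ratio: (*s* × *p*1)/(*s* × *p*0) = *p*1/*p*0, unchanged.

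The protocol gives neither *p* nor *s*, so the loss cannot be put as a number. The algebra covers only this part of the endpoint; clinical events, serious events and laboratory events with an intervention are recorded in any case.

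**Are the values available?** Section 6.4.6 and Appendix B schedule blood count, urea, creatinine and electrolytes at day 7, weekly until discharge, and on days 30 and 60, in every arm. Appendix B adds liver tests on the same days. A screening or baseline value exists for each. Section 10.1 has data from laboratory source documents entered into the trial database. A uniform count therefore needs no new test.

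**The case against.** The best defence is that there is no contradiction. Section 8.1 says only that a laboratory finding can be an adverse event, and it points forward. Section 8.2 is then the specific rule for which findings become events, and 8.3 records those. On that reading the endpoint counts what it says it counts, and the only omission is a cross-reference. This is a fair reading, and it makes the conflict mild. It does not remove the dependence on discretion: under 8.2 alone, the two-investigator example still gives two different counts.

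Four stronger conclusions that a reader might draw are not supported:

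- **That 8.2 excludes abnormalities without intervention.** It sets a minimum and expressly permits reporting of untreated values that suggest organ toxicity.
- **That the endpoint does undercount.** This is possible but not shown, since no rates are given.
- **That the arms are compared with bias.** The trial is double blind and blood tests are scheduled alike in all arms. The text gives no ground for a different recorded share by arm.
- **That power is lost.** Section 9.2 attaches no test to adverse-event frequencies, and any power figure would rest on event rates and recording shares for which the protocol offers no basis.

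The primary safety endpoint is also untouched, because its bleeding definition in section 5.2 has its own haemoglobin criterion that requires no intervention.

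It can also be said that the details of laboratory tables belong in the statistical analysis plan, which is not shown. That is true of layout and programming. The analysis plan cannot, however, reconcile differing instructions to sites, and the definition of the endpoint stands in the protocol.

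**Conclusion.** The point holds in a limited form. A grade 3-4 laboratory value with no intervention and no clinical sequelae counts toward a named secondary safety endpoint only by investigator choice, although 6.4.6 and 8.3 say that all adverse events are recorded. That endpoint may therefore under-ascertain recognised aspirin toxicity, and do so inconsistently. If investigators record the same share in each arm, absolute differences in this component shrink and ratios do not; the amount is unknown. This rests on reading 8.2 as written and needs no assumed event rate. The endpoint is secondary and descriptive and the laboratory values are collected anyway, so this is an inexpensive improvement to the safety evidence and not a threat to the trial's primary conclusions.

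**What to change.** 1. Keep the 8.2 rule for site reporting of clinical adverse events, and have 8.1 and 8.3 refer to it, so that sites have one instruction.
2. State in 5.2 and 9.2 that CTCAE grade 3-4 laboratory abnormalities by day 60 that are worse than baseline are derived, blind to arm, from the laboratory results already collected, whether or not there was an intervention.
3. Report per arm the number of patients with at least one such abnormality, with Wilson intervals and risk differences as section 9.2 already uses for the primary endpoints, beside the recorded adverse events and not in place of them.

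The cost is protocol wording and a little programming, with no extra blood tests and no change to patient care. More events will appear in every arm, many of them due to the disease or the anti-tuberculosis drugs, so the reading should rest on the comparison with placebo. One limit remains: weekly tests stop at discharge, so patients with longer stays have more results in which an abnormality can be found. The number of patients tested at each visit should be shown by arm.

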## Adverse Event Recording

All adverse events which initiate after administration of the first dose of study drug and before the end of study day 60 will be recorded in the CRF. Events which are grade 3 and 4 adverse events and those judged to be possibly related or related to the trial intervention will be followed to resolution.

## Regulatory Reporting of Adverse Events

As serious adverse events and mortality are common in tuberculous meningitis, safety reporting will focus on events of potential relevance to the trial intervention. The following events will be reported to the site ethical committee and the ethical committee of the Viet Nam Ministry of Health:

- All unexpected serious adverse events
- All serious adverse events judged to be related or possibly related to the trial intervention
- All deaths

Reporting to the ethical committees will include an initial written report, which will be sent as soon as possible and within 7 days of occurrence. The format and content of the initial report should follow the Viet Nam Ministry of Health report template and include all information available at the time of reporting. A follow up report with complete details will be sent within 15 days of the initial report if the initial report does not contain the details of event resolution.

## Safety Reporting and the Data Safety and Monitoring Board

An independent Data and Safety Monitoring Board will be established consisting of expert Vietnamese and international researchers and doctors, with the necessary clinical, research and statistical knowledge. The DSMB will review the protocol and agree to a data review schedule and reporting requirements applicable before the study commences, with particular reference to the details of the interim review. A DSMB charter will outline its responsibilities and how it will operate.

The DSMB will perform a safety review of data for the first 30 patients enrolled to the trial. This review will include unblinded summary tables of baseline characteristics, SAEs, AEs and event reports submitted to the DSMB. An analysis of overall clinical outcome will be performed. If deemed necessary, an additional safety review may be performed after the enrolment of 60 patients or annually at the discretion of the DSMB based on available data and ongoing reporting. All DSMB reports will be sent to the responsible ethical committees including the site ethical committees, the Oxford Tropical Research Ethics Committee and the Viet Nam Ministry of Health ethical committee for consideration. Recruitment will continue at any active site during the DSMB review period.

As the dissemination of preliminary summary data could influence the subsequent conduct of the trial and introduce bias, access to interim data and results will be confidential and strictly limited to the DSMB members. No results (except for the recommendation) will be communicated to the outside and/or the clinical investigators involved in the trial.

## Protocol Violations

Protocol violations (PV) are events that contradict or omit protocol instructions and fulfil one or more of the following criteria: 1) the safety/welfare of one or more patients is put at risk by the non-compliance, 2) the integrity of study data is compromised by the violation.

PVs must be reported to the sponsor as soon as possible. If the PI or sponsor confirms that the PV poses a risk to patient safety/welfare or the integrity of study data, the PV must be reported to the responsible hospital Ethical Committee.

# STATISTICS

## Sample size justification

Sample size was chosen based on clinical and feasibility considerations. The calculations below provide evidence of what can be achieved with a sample size of 40 patients per group for the primary safety and efficacy endpoints, respectively.

The proportion of HIV uninfected patients with clinically significant gastro-intestinal bleeding from our on-going 05TB trial of hyper-intensive anti-tuberculosis chemotherapy in Vietnam is about 1% (3/278). Cerebral bleeding associated with TBM is extremely rare (estimated at <0.01% of all patients), but it is possible it may be more common in those treated with aspirin. We have, therefore, included in the primary assessment of safety.

Assuming no effect of aspirin on gastrointestinal bleeding, i.e. a true gastrointestinal bleeding risk of 1% for aspirin, the probability will be 67% to observe 0/40 patients and 27% to observe 1/40 patient experiencing gastrointestinal bleeding in each aspirin arm. The corresponding upper limits of the 95% confidence intervals for the risk of a gastrointestinal bleed would allow “proving” that the true gastrointestinal bleeding risk for aspirin is (at worst) ≤8.8% (in case of 0/40 observed gastrointestinal bleeding) or ≤12.9% (in case of 1/40 observed gastrointestinal bleeding).

Assuming further equal gastrointestinal bleeding risks of 1% in the combined aspirin groups, the probability will be 80% that we observe zero or one bleeding event amongst the 80 patients receiving aspirin and the corresponding upper limit of the 95% confidence interval for the risk of a bleed would allow “proving” that the true overall bleeding risk for aspirin is (at worst) ≤6.8%.

If in contrast, the risk of bleeding was increased to 10% in one of the aspirin arms, the probability would be 78% that we observe 3/40 patients with gastrointestinal bleeding or more with a corresponding 95% confidence interval that would “prove” that the true bleeding risk for that aspirin arm were (at best) ≥2.5%.

We expect a risk of new MRI-proven brain infarction or death within 60 days of approximately 40% in the control arm. Based on the results of the trial performed by Misra et al ^16^, we assume that 81 mg aspirin daily may halve this risk to 20% and the risk in the 1000 mg aspirin daily arm is between 20-40%, then a linear trend test across the 3 groups will have approximately 75% power to detect such an effect at the one-sided 10% significance level (i.e. to generate “mild evidence”) and approximately 50% power to detect it at the conventional one-sided 2.5% significance level.

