***Clinical data supporting a role for aspirin in TBM treatment***

Two recent clinical studies suggest aspirin is safe when added to dexamethasone and may improve outcome from TBM. The first study randomised 118 Indian adults with TBM to standard anti-tuberculosis chemotherapy, with or without aspirin (150mg daily)[^16^](#_ENREF_16). The investigators hypothesised that aspirin would reduce the incidence of stroke and the primary endpoint was MRI-proven infarction by 3 months, with or without neurological deficit. By 3 months, MRI proven stroke occurred in 21 (33.3%) of all patients: 13 (43%) in the placebo arm and 8 (24%) in the aspirin group (P=0.18). Aspirin was associated with a significant reduction in mortality (43% versus 21.7%, P=0.02). The incidence of adverse events was not significantly different between the treatment groups and, in particular, there was no aspirin-associated gastro-intestinal bleeding reported. The results are hard to interpret, however, because of the variable use of prednisolone across the treatment arms. Prednisolone was given for severe disease at baseline, or if a patient’s condition worsened after the start of treatment. Any effect of aspirin, especially on mortality, is hard to disentangle from that of the corticosteroids.

A second study randomised 146 South African children with TBM to standard anti-tuberculosis chemotherapy plus placebo (n=50), low-dose aspirin (75mg/24 hours) (n=47), or high-dose aspirin (100mg/kg/24hours) (n=49) [^17^](#_ENREF_17). Aspirin has no significant impact on survival, but 9 children developed hemiplegia after the start of treatment and none of them received high-dose aspirin. Furthermore, the children in the high-dose aspirin group were significantly younger with more severe disease than the other treatment groups, yet their neurological outcomes were similar. Two children stopped aspirin early: one because of haematemesis and the other because of cerebral haemorrhage. Whether these patients received high or low dose aspirin was not reported.

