### Randomisation and Dosing

Randomisation will be 1:1:1 to 81mg aspirin, 1000mg aspirin and placebo, with stratification by MRC disease severity grade. Subject numbers will be stratified and assigned sequentially as each subject is randomised. Each patient will receive the next sequential package of blinded study drugs which will be prepared in advance and available on the ward. Each treatment pack will contain two bottles of study treatment. One bottle will contain 81mg tablets of aspirin or placebo, the second bottle will contain 500mg tablets of aspirin or placebo. For 60 days, patients will take one 81mg tablet and two 500mg tablets. Administration of the two daily 500mg tablets will be separated by approximately 12 hours.

The first dose of one 81mg tablet and one 500mg tablet will be given as soon as possible after randomisation. One 500mg tablet will be taken approximately 12 hours later. In the case of the first dose being taken late in the day on study day one, the second dose may be given over a shorter time period to ensure the full dose is administered on the first day.

Patients will take medication orally with water if required. Patients unable to swallow will be given crushed tablets via a naso-gastric tube at the same doses.

Patients who vomit within 30 minutes of dosing will be given a replacement dose.

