## Description of Statistical Methods

The risk of clinically significant upper-gastro-intestinal bleeding and image-proven cerebral bleeding by 60 days will be summarized as x/n (%) in each group together with two-sided 95% Wilson confidence intervals and corresponding confidence intervals for risk differences between groups.

The risk of the primary efficacy endpoint of new MRI-proven brain infarction or death by 60 days will be summarized in the same way. In addition, we will perform a linear trend test for group differences based on logistic regression with adjustment for gender, MRC grade, and age.

The risk of disability or death will be summarized as for the primary efficacy endpoint and the analysis of overall survival during 240 days will be based on Kaplan-Meier graphs and Cox regression. The frequency of adverse events in each study arm and resolution of CSF inflammation will be analysed descriptively.

Analyses to explore the effect of LTA4H genotype will include this information as an additional covariate in the regression models.

As this is a pilot study of relatively small size and limited power, p-values will be interpreted with caution and a one-sided p-value <0.1 will be regarded as mild evidence for an effect. Corresponding two-sided 95% confidence intervals will be provided for all tests to assess the range of plausible magnitudes of effects given the data.

No imputation of missing data will be performed. For the analysis of GI/cerebral bleeding by day 60, patients lost to follow-up before day 60 (without prior GI bleeding) will be excluded from the analysis to get a conservative estimate of the true proportion of bleeding in the aspirin groups. The analysis of the primary efficacy endpoint will exclude patients with missing baseline or follow-up MRI scans (except for prior death).

All analyses will analyze patients according to their randomized treatment group.

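### The primary efficacy trend test has no stated arm order or scores, and its quoted 75%/50% power holds over the assumed range only if the arms are not taken in dose order

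*Protocol*

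**What the plan says.** Protocol section 9.1 describes what can be achieved with "a sample size of 40 patients per group for the primary safety and efficacy endpoints". Allocation is equal (section 6.4.5: "Randomisation will be 1:1:1 to 81mg aspirin, 1000mg aspirin and placebo"). For efficacy, 9.1 states: "We expect a risk of new MRI-proven brain infarction or death within 60 days of approximately 40% in the control arm". It then says "we assume that 81 mg aspirin daily may halve this risk to 20" per cent, and continues: "the risk in the 1000 mg aspirin daily arm is between 20-40%, then a linear trend test across the 3 groups". For this whole set of risks it gives that test one pair of power figures: about 75% at one-sided 10% and about 50% at one-sided 2.5%.

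Section 9.2 first summarises the efficacy endpoint by arm, with Wilson intervals and confidence intervals for risk differences between groups. In addition, it says, "we will perform a linear trend test for group differences based on logistic regression with adjustment for gender, MRC grade, and age". A one-sided p-value below 0.1 will count as mild evidence of an effect.

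Neither section says in what order the three arms enter the trend or which scores they carry.

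**The concern.** The arms are three quantities of one drug (0, 81 and 1000 mg), and section 5.1 lists them in that sequence. Most readers would therefore take a linear trend across them to mean dose order. The assumed risks do not fit that reading. Running from 40% to 20% to somewhere between 20% and 40%, they are flat above 81 mg at best and otherwise turn back up. A trend test with equally spaced scores compares the two end groups, so in dose order it compares placebo with 1000 mg and gives no weight in the contrast to the arm assumed to work.

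This is the only hypothesis test that the protocol names for the primary efficacy endpoint. If order and scores are left open, the power statement cannot be interpreted, two analysts could run different tests under the same text, and the order could be chosen after the data are seen.

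**Working it through.** **Inputs.** 40 patients per arm (9.1); equal allocation (6.4.5); risks of 40% on placebo, 20% on 81 mg and p on 1000 mg, with p from 20% to 40% (9.1); one-sided 10% and 2.5% (9.1). Assumptions of this check: all 40 per arm evaluable, no covariate adjustment.

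**Formula.** Cochran-Armitage trend test with scores 0, 1, 2, so centred scores −1, 0, 1:

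- expected contrast U = n × (risk in first group − risk in last group)
- null variance V0 = 2n × m(1 − m), with m the mean of the three risks
- variance under the alternative V1 = n × [sum of risk × (1 − risk) over the first and last groups]
- power = Φ[(U − z√V0)/√V1], with z = 1.2816 (10%) or 1.960 (2.5%)

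**Reproducing the plan's figure.** Take the order placebo, 1000 mg, 81 mg, with p = 30%:

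- U = 40 × (0.40 − 0.20) = 8; m = 0.30
- V0 = 80 × 0.21 = 16.8, √V0 = 4.099; V1 = 40 × (0.24 + 0.16) = 16, √V1 = 4
- 10%: Φ[(8 − 5.253)/4] = Φ(0.687) = 75.4%
- 2.5%: Φ[(8 − 8.034)/4] = Φ(−0.008) = 49.7%

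These are the printed 75% and 50%.

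**Same risks, dose order** (placebo, 81 mg, 1000 mg), p = 30%:

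- U = 40 × (0.40 − 0.30) = 4; V0 = 16.8; V1 = 40 × (0.24 + 0.21) = 18, √V1 = 4.243
- 10%: Φ[(4 − 5.253)/4.243] = Φ(−0.295) = 38.4%
- 2.5%: Φ[(4 − 8.034)/4.243] = Φ(−0.951) = 17.1%

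**Over the assumed range** (power at one-sided 10% / 2.5%):

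| 1000 mg risk | Order placebo-1000-81 | Dose order |
|---|---|---|
| 20% | 76.8 / 52.5 | 76.8 / 52.5 |
| 25% | 76.1 / 51.0 | 58.0 / 32.3 |
| 30% | 75.4 / 49.7 | 38.4 / 17.1 |
| 35% | 74.8 / 48.5 | 22.0 / 7.7 |
| 40% | 74.2 / 47.4 | 10.9 / 3.0 |

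Simulation of the same test (200,000 trials per cell) agrees within about 1 point. Simulated unadjusted logistic trend tests (3,000 trials, p = 20, 30 and 40%) agree within about 3 points.

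**Scores matter within dose order too.** With the actual milligrams as scores, power runs from 51.3/24.8% down to 1.4/0.2% over the range. With log(1 + dose) it runs from 80.9/58.5% down to 18.3/6.0%.

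**What the non-dose order gives up.** In the order placebo, 1000 mg, 81 mg, suppose that 1000 mg halves the risk to 20% while 81 mg is at 30% or 40%. The end groups are then 40% v 30% or 40% v 40%, and power is 38.4/17.1% or 10.9/3.0%.

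**Placebo v 81 mg alone.** 40% v 20% with 40 per arm has U = 8, V0 = 80 × 0.21 = 16.8 and V1 = 16. Power is 75.4/49.7%, whatever happens on 1000 mg. At one-sided 5% it is Φ[(8 − 1.645 × 4.099)/4] = Φ(0.314) = 62.3%.

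**Error cost of two tests.** Two comparisons sharing a placebo arm of equal size have correlation 0.5 under the null. The chance that at least one is falsely positive is 16.8% with each at one-sided 10%, and 8.8% with each at one-sided 5%.

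**The case against.** The strongest reply is that the printed power is right. The protocol never says dose order, and quoting one figure for a 20-40% range makes sense only if the 1000 mg arm sits in the middle. Under that order the figures reproduce within about 3 points. This stands: a reader might infer that the test lacks its stated power, and the document does not support so flat a claim. The 11/3% figure also needs both dose order and no effect at all of 1000 mg.

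It can also be said that a halving of risk on 1000 mg alone lies outside the assumptions, since 9.1 fixes 81 mg at 20%. That too stands: low power there is a matter of robustness, not a mistake in the calculation. The background cuts both ways. It places anti-inflammatory effects at 1 g daily or more and reports from a paediatric trial that "9 children developed hemiplegia after the start of treatment and none of them received high-dose aspirin", but that trial dosed high-dose children by weight, and the background gives low-dose aspirin a rationale of its own. The protocol's own question 3 (section 3) asks which dose is likely to be the more effective, so an order that ranks 81 mg as the better presumes the answer.

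A reader might go further and infer that the primary objective goes untested. The objective in 4.1 is to generate pilot data on each dose against no aspirin, and 9.2 already plans risk-difference intervals between groups. The trend test comes on top of these, so that inference fails.

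Finally, scores are often left to a statistical analysis plan, and one may exist. It could fix the analysis, but the power statement in 9.1 would still be unreadable without the order.

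**Conclusion.** The trend test is under-specified, and its quoted power depends on an unstated order that is not dose order. Within the protocol's own assumptions, power at one-sided 10% stays between 77% and 74% in the order placebo, 1000 mg, 81 mg, but runs from 77% down to 11% in dose order with equal spacing. At one-sided 2.5% the ranges are 53% to 47% and 53% to 3%. The conclusion rests on 40 evaluable patients per arm and an unadjusted test. Section 9.2 excludes patients with a missing baseline or follow-up MRI (other than prior deaths), so actual power will be somewhat lower under either order.

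This should be fixed but is not critical. The sample size was set on clinical and feasibility grounds, p-values are to be read with caution, and each dose is already compared with placebo by interval estimates.

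**What to change.** - **Section 9.2:** enter arm as a three-level factor in the same logistic model (adjusted for gender, MRC grade and age) and test each dose against placebo, alongside the risk-difference intervals already planned.
- **Section 9.1:** attribute the power to that comparison: 40% v 20% with 40 per arm, about 75% at one-sided 10% and about 50% at one-sided 2.5%, before exclusions for missing MRI. The printed figures then stand whatever the other dose does.
- **If the trend test is kept:** state its order and scores in both sections, before unblinding, and give its power as a range over the 20-40% assumption.

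The cost is wording only; no patients, visits or data are added. The statistical price is that two tests at one-sided 10% raise the chance of at least one false finding of mild evidence from 10% to about 17%. Running each at one-sided 5% holds it to about 9%, but power for 40% v 20% then falls to about 62%. The protocol should say which of these is accepted.
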